### **10.3. Withdrawal From the Study**

A subject will be withdrawn from the study for any of the following reasons:

- lost to follow-up
- withdrawal of consent (subjects who withdraw consent should be treated appropriately).

In case a subject is lost to follow-up, every possible effort must be made by the study site personnel to contact the subject and determine the reason for discontinuation. The measures taken to follow up must be documented.

When a subject withdraws before completing the study, the reason for withdrawal is to be documented on the CRF and in the source document. Study drug assigned to the withdrawn subject may not be assigned to another subject. Subjects who withdraw will not be replaced.

## 11. STATISTICAL METHODS\*

### 11.1. Sample Size Determination

The sample size determination is based on a noninferiority test of ceftobiprole versus the comparator in terms of the primary efficacy parameter, clinical cure rate. The assumptions on which the sample size estimate is based are as follows:

- Clinical cure rates of 90% for both randomized study treatments ceftobiprole and the comparator
- Limit of noninferiority of ceftobiprole versus the comparator is 10%
- Type 1 error probability ( $\alpha$ ) = 0.05 (2 sided)
- Type 2 error probability ( $\beta$ ) = 0.2 (power = 0.8 = 1 –  $\beta$ )
- The evaluable rate is 80%.

Based on these assumptions, 670 subjects will need to be randomized to ensure 532 clinically evaluable subjects, 266 subjects in each treatment group.

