## Hypotheses

### Efficacy:

The clinical cure rate, with respect to treatment with ceftobiprole with/without switch to oral therapy, will be noninferior to a regimen of the comparator, with/without a switch to oral therapy, in the clinically evaluable subjects hospitalized with CAP.

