### 3.1. Study Design\*

This randomized, double-blind, comparator-controlled, multicenter study is designed to assess the efficacy and safety of ceftobiprole compared with the comparator in subjects 18 years of age or older with CAP of sufficient severity to require hospitalization and treatment with i.v. antibiotics for a minimum of 3 days (72 hours). The study will consist of a prerandomization phase (baseline), a double-blind treatment phase with an end-of-treatment (EOT) visit (within 48 hours after the end of therapy), and a follow-up phase with a TOC/early termination visit 7 to 14 days after the last dose of study drug, and a LFU visit 28 to 35 days after the last dose of study drug. The total duration of the study participation for a subject will be up to 49 days.

---

\* This section of the protocol has been revised. Please refer to the section of this document entitled PROTOCOL AMENDMENTS (Amendment INT-3, 22 December 2006) for a detailed description of the specific changes.

Approximately 670 subjects will be randomized to achieve 266 clinically evaluable subjects receiving ceftobiprole and 266 clinically evaluable subjects receiving the comparator. This trial will be conducted in a manner to ensure that investigators, those administering study drug, and subjects are blinded to treatment regimen. Placebo will be used to maintain the blind for both the cephalosporin (ceftobiprole and ceftriaxone) and linezolid therapies. Central randomization will be used to randomly assign subjects in a 1:1 ratio to receive ceftobiprole or the comparator. Subjects will be stratified by the Pneumonia Outcomes Research Trial (PORT) Severity Index (PSI) score at randomization ( $PSI \leq 90$  versus  $PSI \geq 91$ ; see Attachment 1, PORT Severity Index [PSI]). Subjects will also be stratified by the need for anti-staphylococcal therapy (placebo or linezolid) based on signs, symptoms, and medical history at enrollment.

All subjects should receive a minimum of 3 days (72 hours) of the i.v. study drug(s) and should continue to receive i.v. therapy while hospitalized (see Section 6, Dosage and Administration). At the discretion of the investigator, subjects may receive study drug infusions as outpatients or through a home-care agency, provided they meet all other protocol requirements, but all i.v. study drug infusions must be administered and monitored by a qualified nurse, a qualified member of the study staff, or an infusion specialist.

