**11.3.4. Analysis of Primary Parameter**

The primary analysis of clinical cure rate will be based on the CE population and the ITT population as coprimary populations.

A noninferiority hypothesis will be assessed based on clinical cure rates at the TOC visit. The hypotheses will be:

- $H_0$ : The clinical cure rate of ceftobiprole is more than 10% inferior to that of the comparator.
- $H_1$ : The clinical cure rate of ceftobiprole is not more than 10% inferior to that of comparator.

This hypothesis will be operationally tested by presenting the 2-sided 95% confidence limits of the between treatment difference in clinical cure rate at the TOC visit. In order to claim noninferiority, the lower bound of the 2-sided 95% confidence interval must be  $\geq -10\%$ .

In addition, clinical outcome at the TOC visit will be summarized descriptively by initial pathogen, subject subgroups defined by age (<65 versus ≥65 years), by sex (men versus women), and by race.

The analysis of clinical cure rate will be performed in the mITT populations as well. Subjects in the ITT and mITT populations whose clinical outcome is assessed as missing or Not Evaluable, will be included in the analysis of clinical outcome as failures.

Exploratory analyses of clinical outcome (cure versus failure) based on logistic regression models adjusting for geographical region and baseline factors may be performed.

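### The assumptions listed in Section 11.1 give 142 evaluable subjects per arm, not 266; 266 gives about 97% power in the CE population, and the ITT assumption that could justify 670 is never stated

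*Protocol*

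**What the plan says.** Protocol Section 11.1 sets out five planning assumptions:

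- "Clinical cure rates of 90% for both randomized study treatments ceftobiprole and the comparator";
- a noninferiority limit of 10%;
- type 1 error of 0.05, two-sided;
- type 2 error of 0.2, so 80% power;
- an evaluable rate of 80%.

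It then concludes: "Based on these assumptions, 670 subjects will need to be randomized to ensure 532 clinically evaluable subjects, 266 subjects in each treatment group". The Statistical Methods part of the Synopsis repeats the assumptions and the conclusion. Section 3.1 fixes equal allocation: "Central randomization will be used to randomly assign subjects in a 1:1 ratio to receive ceftobiprole or the comparator".

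Section 11.3.4 defines the analysis that this size must serve: "The primary analysis of clinical cure rate will be based on the CE population and the ITT population as coprimary populations". For the ITT and mITT populations, it says that subjects "whose clinical outcome is assessed as missing or Not Evaluable, will be included in the analysis of clinical outcome as failures". Noninferiority is to be claimed when the lower limit of the two-sided 95% interval is at or above -10%. The rule is given once, without naming the population or populations in which it must hold. The efficacy hypothesis in Section 2, and in the Synopsis, is worded only for noninferiority "in the clinically evaluable subjects hospitalized with CAP".

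**The concern.** Section 11.1 presents 266 per arm as the result of the listed inputs. A reader who repeats the calculation gets little more than half that number. So either an input is misreported or the size was set by something the section leaves out. As printed, the power attached to the CE population is wrong, and the sample size has no derivation that can be checked.

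The omission matters because ITT is coprimary and its cure rate must be lower than the CE rate whenever non-evaluable subjects count as failures. A lower cure rate has a larger variance, so ITT is the more demanding of the two analyses. Its power depends on a cure rate that Section 11.1 does not give.

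The CE-only hypothesis is a second, smaller matter: it does not match the two-population primary analysis.

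**Working it through.** **Inputs.** From Section 11.1: cure p = 0.90 in both arms, margin 0.10, one-sided alpha 0.025 (two-sided 0.05), power 0.80, evaluable rate 0.80. From Section 3.1: 1:1 allocation. From Section 11.3.4: CE and ITT coprimary, with missing or Not Evaluable counted as failure in ITT.

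**Step 1: try to reproduce 266.** The usual noninferiority formula for two proportions is

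n per arm = (z₀.₉₇₅ + z₀.₈₀)² × 2p(1 − p) / margin² = (1.960 + 0.842)² × 0.18 / 0.01 = 141.3, so 142.

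That is 284 CE subjects, and 284 / 0.8 = 355 randomized (356 if rounded up by arm). The printed 266 is about 1.9 times 142.

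Variants at 80% power, per arm:

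| Variant | n per arm |
|---|---|
| One-sided alpha 0.05 | 112 |
| Farrington-Manning | 155 |
| Continuity correction | 162 |
| One-sided alpha 0.0125 | 172 |
| Equivalence (two one-sided tests, beta/2) | 190 |
| 90% versus 80% as a difference test, unpooled | 197 |
| Same, pooled | 199 |
| Same, with continuity correction | 219 |

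None gives 266. A superiority formula for 90% versus 80% does give 266, but only at 90% power, which is not what the section states.

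**Step 2: check the inflation.** 532 / 0.8 = 665, consistent with approximately 670. The discrepancy therefore lies in 266 itself, not in the step to 670.

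**Step 3: CE power at 266 per arm.**

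Φ(0.10 / √(0.18/266) − 1.960) = Φ(3.844 − 1.960) = 0.970. An exact binomial calculation with a Wald interval gives 0.969.

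**Step 4: ITT power at 335 per arm.** The protocol gives no ITT cure rate, so one must be assumed. If all of the 20% non-evaluable subjects count as failures, the rate is 0.90 × 0.80 = 0.72. Then

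Φ(0.10 / √(2 × 0.72 × 0.28 / 335) − 1.960) = Φ(2.882 − 1.960) = 0.822.

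| Assumed ITT cure rate | ITT power, 335 per arm |
|---|---|
| 72% | 82% |
| 75% | 85% |
| 80% | 90% |
| 85% | 95% |

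**Step 5: joint power.** In 400,000 simulated trials, each of 335 subjects per arm was evaluable with probability 0.80 and, if evaluable, cured with probability 0.90; all others were ITT failures. Using Wald intervals, the bound was met in CE in 97.1%, in ITT in 82.2% and in both in 81.3%. With a continuity-corrected interval, ITT power is 79.9% and joint power about 79%.

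**Step 6: could ITT explain 670?** At 72%, 80% ITT power needs 317 per arm (634 in all), or 337 per arm (674) with continuity correction. The second figure is close to 670.

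**The case against.** The strongest reply is that 670 is a sound number and only its explanation is at fault. The Amendment INT-1 entry in the amendment log gives the reason for moving to 1:1 and from 500 to 670: enough power for the primary endpoint in both CE and ITT. On the 72% assumption, ITT and joint power come out near 80%, so 80% approximately describes the requirement that both populations pass. This stands. It does not rescue Section 11.1, which ties 266 to CE subjects and to CE assumptions and carries neither the ITT reason nor an ITT rate. The log gives no figure either, and it shows that 266 was already the ceftobiprole number under the previous 266/133 split. The ITT explanation is therefore plausible, not documented.

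It also stands that 72% is an inference. Section 11.3.1 links CE exclusion to dosing and to less than 5 days of treatment as well as to outcome. A subject outside CE for short treatment but rated cured would be an ITT cure. Given 90% cure among evaluable subjects and 80% evaluable, 72% is therefore a floor, and ITT power could be higher, as the range shows.

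Three stronger readings are tempting and are not supported:

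- A reader might infer that the trial is underpowered or that N must change. CE power exceeds the stated 80%, and ITT and joint power are about on target at the floor of the assumed ITT rate.
- A reader might infer that passing in one population is enough. Nothing in the protocol says so. Naming CE and ITT as coprimary favors requiring both, and the primary objective in Section 2 is not limited to CE; only the hypothesis sentence is.
- A reader might simulate CE cure of 80% versus 90%, find claim rates of 8.0% for ITT alone and 9.1% if either population sufficed, and call these inflated type 1 error. With 80% evaluable in both arms, the ITT difference is then 0.64 − 0.72 = −8 points, inside the margin. They are errors with respect to the CE null only.

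**Conclusion.** The derivation is wrong as written, in Section 11.1 and in the Synopsis. The listed assumptions yield 142 CE subjects per arm (112 to 219 across the variants tried), not 266, and 266 per arm carries about 97% CE power instead of 80%. This rests only on figures that the protocol states.

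The size itself is defensible. At 335 per arm, ITT power is about 82% and joint power about 81% if every non-evaluable subject is an ITT failure, and ITT power is higher if some are cures. These figures depend on equal true cure rates, 80% evaluable in both arms and an ITT cure rate that the sponsor has not stated. The gap is the missing ITT assumption and the missing ITT and joint power.

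The mismatch between the CE-only hypothesis and Section 11.3.4 is a secondary point of alignment.

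**What to change.** Keep 670 randomized.

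1. In Section 11.1 and the Synopsis, remove the statement that 266 per arm follows from the listed assumptions. Replace it with: CE power of about 97% at 266 per arm and 90% cure; the ITT cure rate that the sponsor assumes, with its basis; and the resulting ITT and joint power at 335 per arm. The 72%, 82% and 81% figures illustrate the form of the statement. They should be printed only if the sponsor adopts that assumption.
2. Reword the efficacy hypothesis in Section 2 and the Synopsis so that it covers CE and ITT, as Section 11.3.4 does.
3. In Section 11.3.4 and the Synopsis, state that noninferiority is claimed only if the lower bound is at least -10% in both CE and ITT.

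The cost is wording only: no change to sample size, margin, populations or data collection.

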### 11.2. Pharmacokinetic Analyses

Within each subject group, individual and overlay plasma concentration-time profiles of ceftobiprole will be plotted on both linear and log scales. Mean and median plasma concentration-time profiles will be graphically presented for each subject group. Plasma and urine concentration data at each time point will be summarized per subject group with mean, median, standard deviation, minimum value, maximum value, and coefficient of variation (%).

All estimated plasma and urine PK parameters of ceftobiprole will be summarized per subject group with mean, median, geometric mean, minimum value, maximum value, standard deviation, and coefficient of variation (%).

---

\* This section of the protocol has been revised. Please refer to the section of this document entitled PROTOCOL AMENDMENTS (Amendment INT-3, 22 December 2006) for a detailed description of the specific changes.

## **11.3. Analyses Methods\***

### **11.3.1. Definition of Populations**

The following subject populations will be defined for the analyses:

Intent-to-Treat (ITT) Population: The set of all randomized subjects.

Modified Intent-to-Treat (mITT) Population: The subset of randomized subjects with a confirmed pathogen in baseline samples.

Clinically Evaluable (CE) Population: The subset of the ITT population who received at least 1 dose of study drug, excluding those subjects with a clinical outcome of Unable to Evaluate at the TOC visit and who have <5 days of study treatment. Those who have at least 2 days of treatment but who are judged as clinical failures will be evaluable.

Microbiologically Evaluable (ME) Population: All randomized subjects who received at least 1 dose of study drug with a confirmed pathogen in baseline sample, excluding those subjects with a microbiological outcome of Unable to Evaluate at the TOC visit.

Safety Population: All randomized subjects who are exposed to study drug.

### **11.3.2. Definition of Parameters**

#### **Primary**

- Clinical cure rate, defined as the ratio of the number of clinically cured subjects to the total number of subjects in the population, at TOC visit.

#### **Secondary**

- Microbiological eradication rate, defined as the ratio of the number of subjects with microbiological eradication or presumed eradication to the total number of subjects in the population at TOC visit.
- Clinical cure rate following treatment with ceftobiprole versus the comparator of hospitalized CAP subjects that require mechanical ventilation within the first 48 hours of enrollment

---

\* This section of the protocol has been revised. Please refer to the section of this document entitled PROTOCOL AMENDMENTS (Amendment INT-3, 22 December 2006) for a detailed description of the specific changes.

- Microbiological eradication rate following treatment with ceftobiprole versus the comparator of hospitalized CAP subjects that require mechanical ventilation within the first 48 hours of enrollment.
- Clinical and microbiological relapse at LFU visit
- Thirty-day pneumonia-specific mortality rates following treatment with ceftobiprole or the comparator.

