## 2. OBJECTIVES

The primary objective is to demonstrate the noninferiority of ceftobiprole medocaril compared with ceftriaxone with/without linezolid (comparator) with respect to the clinical cure rate in subjects hospitalized with CAP at the TOC visit.

The secondary objectives are:

- To compare the microbiological eradication rate following treatment with ceftobiprole versus the comparator in subjects with hospitalized CAP at the TOC visit
- To compare the clinical cure rate following treatment with ceftobiprole versus the comparator of hospitalized CAP subjects that require mechanical ventilation within the first 48 hours of enrollment
- To compare the microbiological eradication rate following treatment with ceftobiprole versus the comparator of hospitalized CAP subjects that require mechanical ventilation within the first 48 hours of enrollment
- To compare the clinical and microbiological relapse rates following treatment with ceftobiprole versus the comparator in subjects with hospitalized CAP at the late follow-up (LFU) visit

To compare the 30-day pneumonia-specific mortality rates following treatment with ceftobiprole or the comparator of hospitalized CAP subjects

Other objectives are:

- To assess the PKs of ceftobiprole in subjects treated with ceftobiprole
- To collect medical resource utilization (MRU) data that may be used in future economic modeling

Safety/tolerability objectives are:

- To characterize the safety and tolerability of treatment with ceftobiprole in subjects hospitalized with CAP

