#### **Disease Specific**

Subjects with CAP severe enough to require hospitalization and treatment with i.v. antibiotics for at least 3 days (72 hours) defined as follows:

- Subjects must have a, b, c, d, AND e
  - a) Clinical diagnosis of acute bacterial pneumonia acquired in the community. Subjects must have resided in the community (i.e., NOT in a chronic care facility such as a nursing home or rehabilitation facility) and NOT have been hospitalized during the 14 days before the onset of

symptoms of pneumonia. Residence in an assisted-living facility where the subject has regular access to the community is allowed.

- b) Clinical signs or symptoms of acute bacterial pneumonia with AT LEAST 2 of the following criteria:
- Cough (new or increased over usual state)
  - Production of purulent sputum or a worsening in the character of sputum
  - Auscultatory findings on pulmonary examination of rales or evidence of pulmonary consolidation (dullness on percussion, bronchial breath sounds, or egophony)
  - Dyspnea or tachypnea (respiratory rate  $\geq 20$  breaths per minute), that is new or worse than usual state
  - New onset hypoxemia on room air ( $PO_2 < 60$  mmHg on arterial blood gas or  $O_2$  saturation  $< 90\%$  by pulse oximetry), or respiratory failure requiring mechanical ventilation.
- c) New radiographic infiltrates (not related to another disease process) consistent with the diagnosis of bacterial pneumonia
- d) Fever or leukocytosis/leukopenia (temporally associated with the onset of pneumonia symptoms) with AT LEAST 1 of the following:
- Fever (in the absence of antipyretics) defined as an axillary temperature  $> 37.5^\circ\text{C}$ , oral temperature  $> 38^\circ\text{C}$ , a tympanic temperature  $> 38.5^\circ\text{C}$ , a rectal temperature  $> 39^\circ\text{C}$ , OR hypothermia, defined as a rectal body temperature of  $< 35^\circ\text{C}$ .
  - Leukocytosis defined as an elevated total peripheral WBC count  $\geq 10 \times 10^9/\text{L}$  or  $\geq 15\%$  immature neutrophils (bands), regardless of total peripheral white count; OR leukopenia with total WBC  $\leq 4.5 \times 10^9/\text{L}$ .
- e) Severity of pneumonia requiring i.v. antibiotic therapy.

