## 6. DOSAGE AND ADMINISTRATION

### 6.1.1. Overview\*

The unblinded pharmacist will be responsible for preparation of the study drug for each subject in such a way that investigators and staff remain blinded to the study drug being administered. Colored sleeves will cover infusion bags and line tubings as needed to maintain the blind. The study drug regimen is discussed in Section 6.1.2, Intravenous and Oral Switch Study Drug Regimen and Section 6.1.3, Linezolid/Placebo Therapy for ceftriaxone-resistant *S. pneumoniae* and *S. aureus*.

All subjects should receive the first dose of study drug as quickly as possible after randomization. In order to ensure subject safety and to avoid potential overdose, if a subject has received a nonstudy antibiotic before enrollment, the timing of the first dose of study drug may be delayed so it is consistent with the recommended dosing interval of the nonstudy antibiotic. In the event that a subject received a nonstudy, beta-lactam antibiotic (e.g., penicillin, cephalosporin, carbapenem) before enrolling in the study, the timing of the first dose of study cephalosporin (ceftobiprole or ceftriaxone) may be delayed. All subjects should receive a minimum of 3 days (72 hours [9 doses of ceftobiprole or 3 doses of ceftriaxone; with placebo administered as described below to maintain the blind]) of the i.v. study drug and should continue on i.v. therapy while hospitalized. At the discretion of the investigator, subjects may receive study drug infusions as outpatients or through a home-care agency, provided they meet all other protocol requirements, but all i.v. study drug infusions must be administered and monitored by a qualified nurse, a qualified member of the study staff, or an infusion specialist. If after 3 days (72 hours) the subject's signs and symptoms have improved from baseline as defined in the protocol and the subject will be discharged from the hospital, the i.v. therapy may be discontinued at the investigator's discretion and the subject treated with oral cefuroxime axetil 500 mg every 12 hours.

---

\* This section of the protocol has been revised. Please refer to the section of this document entitled PROTOCOL AMENDMENTS (Amendment INT-3, 22 December 2006) for a detailed description of the specific changes.

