#### **9.1.3. Double-Blind Treatment Phase**

The total duration of study drug therapy (i.v. plus oral) for all subjects will be a minimum of 5 days and a target of 7 days. If, in the investigator's opinion, a subject requires additional days of study therapy, the duration of the therapy may be extended (up to a maximum of 10 days) (see Section 6, Dosage and Administration).

If by Day 3, a subject has resolution of signs and symptoms of pneumonia (including fever, WBC, tachypnea, chest X-ray), therapy can be discontinued after all doses on Day 5.

If a subject has a positive blood culture at baseline, they must remain on i.v. study drug for a minimum of 5 days pending results of repeat blood cultures.

Administration of study drug(s) beyond 7 days is recommended only for subjects with persistent signs and symptoms consistent with active infection. These criteria include fever  $\geq 38.3^{\circ}\text{C}$ , circulating WBC count greater than  $10,000 \text{ mm}^3$ , lack of improvement on chest X-ray, continued purulent sputum, or bacteremia at enrollment and at least one positive blood culture on therapy.

If more than 10 days are necessary to complete treatment, therapy may be further extended to a maximum of 14 days for subjects with a history of persistent bacteremia or necrotizing pneumonia.

Dosing will begin on Day 1 after baseline assessments are completed. Subjects will have daily assessments while in the hospital to ensure adequate clinical progress and to ascertain appropriateness for change to oral medication and discharge if desired.

Subjects with serum sodium levels outside of the normal range at baseline or during the study should have their electrolytes measured on a daily basis or more often as clinically indicated until the serum sodium level is within the normal range.

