### **Secondary Endpoints**

- Microbiological eradication rate at TOC visit
- Clinical cure rate in subjects requiring mechanical ventilation within 48 hours of enrollment
- Microbiological cure rate in subjects requiring mechanical ventilation within 48 hours of enrollment

---

\* This section of the protocol has been revised. Please refer to the section of this document entitled PROTOCOL AMENDMENTS (Amendment INT-3, 22 December 2006) for a detailed description of the specific changes.

- Clinical and microbiological relapse at LFU visit
- Thirty-day pneumonia-specific mortality rates (all deaths due to pneumonia within 30 days after randomization).

For the definition of these parameters see Section 11.4.2, Definition of Parameters.

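### Two secondary comparisons are confined to subjects ventilated within 48 hours of enrollment, a group that treatment can alter, so randomization does not protect them

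*Protocol*

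**What the plan says.** Section 2 sets a between-arm objective: "To compare the clinical cure rate following treatment with ceftobiprole versus the comparator of hospitalized CAP subjects that require mechanical ventilation", with a 48-hour limit counted from enrollment. A parallel objective covers microbiological eradication. Section 11.3.2 defines both parameters in "hospitalized CAP subjects that require mechanical ventilation within the first 48 hours of enrollment". Section 9.4 lists "Clinical cure rate in subjects requiring mechanical ventilation within 48 hours of enrollment", and the Synopsis carries the same group in its objectives and its efficacy criteria.

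Three other places fix the timing and the population:

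- The Time and Events Schedule puts randomization at the predose Day 1 visit.
- Section 9.1.3 states: "Dosing will begin on Day 1 after baseline assessments are completed". Section 6.1.1 adds: "All subjects should receive the first dose of study drug as quickly as possible after randomization". It allows a delay when a nonstudy antibiotic was given beforehand.
- Section 4.2 allows "respiratory failure requiring mechanical ventilation" as one alternative within one of the five clinical signs, of which any two suffice. Subjects already ventilated at entry can therefore be enrolled.

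Nothing in the protocol limits the subgroup to subjects ventilated before dosing. Section 5.2 stratifies by PSI score and by need for anti-staphylococcal therapy, not by ventilation.

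**The concern.** A subgroup comparison keeps the protection of randomization only if membership is settled before treatment can act. Here membership stays open for 48 hours. A subject who worsens and is intubated at hour 36 joins the subgroup; a similar subject who responds to the assigned drug does not. If the two regimens differ in early deterioration, the ventilated subjects in each arm are different mixtures of people ventilated at entry and people ventilated on treatment. If those two kinds of subject also differ in prognosis, their cure rates will differ between arms even when the drugs have the same effect on cure.

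Two listed secondary objectives rest on this comparison. They concern the sickest subjects, so the result is likely to be read as evidence in severe pneumonia.

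**Working it through.** The protocol gives no figure for this subgroup, so there is nothing to reproduce. The check has three parts.

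**1. How much of the window is on treatment.** Section 6.1.1 counts "9 doses of ceftobiprole or 3 doses of ceftriaxone" in 72 hours. Over 48 hours that is 9 × 48/72 = 6 ceftobiprole doses or 3 × 48/72 = 2 ceftriaxone doses, if dosing starts promptly. If the first dose were delayed by 12 hours (assumed), 36 of the 48 hours would remain on treatment; with a 24-hour delay (assumed), 24 hours.

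**2. What selection alone can do.** Let *b* be the proportion ventilated before the first dose, with cure rate *p_b*. Let *c* be the proportion newly ventilated by 48 hours in the comparator arm, with cure rate *p_n*. Let *r* be the ratio of new ventilation, ceftobiprole to comparator. Cure rates by type are set equal in both arms, so treatment changes nobody's cure.

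- Comparator subgroup cure = (b·p_b + c·p_n)/(b + c)
- Ceftobiprole subgroup cure = (b·p_b + r·c·p_n)/(b + r·c)

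All rates are assumptions; none comes from the protocol: *b* 2 to 10%, *c* 2 to 4%, *p_b* 70%, *p_n* 40 or 80%, *r* 0.5 to 1.5. With b = c = 2%:

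| p_n | r | Comparator | Ceftobiprole | Spurious difference |
|---|---|---|---|---|
| 40% | 0.5 | (0.014 + 0.008)/0.04 = 55.0% | (0.014 + 0.004)/0.03 = 60.0% | +5.0 points |
| 40% | 1.5 | 55.0% | (0.014 + 0.012)/0.05 = 52.0% | -3.0 points |
| 80% | 0.5 | (0.014 + 0.016)/0.04 = 75.0% | (0.014 + 0.008)/0.03 = 73.3% | -1.7 points |
| 80% | 1.5 | 75.0% | (0.014 + 0.024)/0.05 = 76.0% | +1.0 point |
| 40% or 80% | 1.0 | 55.0% or 75.0% | the same | 0 |

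Over the whole assumed grid the range is -3.0 to +5.0 points.

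The sign depends on which group has the better prognosis. Suppose 10 subjects per arm are ventilated at entry, and 15 more become ventilated on one drug but 5 on the other (all assumed). With 50% cure for those ventilated at entry and 70% for the newly ventilated, the arm with more deterioration shows (5 + 10.5)/25 = 62% against (5 + 3.5)/15 = 57%. With the two cure rates exchanged it shows (7 + 7.5)/25 = 58% against (7 + 2.5)/15 = 63%.

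If membership is fixed before the first dose, *c* drops out, both formulas reduce to *p_b*, and the spurious difference is 0.

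**3. Precision.** Central randomization will "randomly assign subjects in a 1:1 ratio to receive ceftobiprole or the comparator", so 670/2 = 335 subjects per arm. In the first table row the subgroup would hold 335 × 0.04 = 13.4 comparator and 335 × 0.03 = 10.05 ceftobiprole subjects. The 95% half-width is 1.96 × √(0.55 × 0.45/13.4 + 0.60 × 0.40/10.05) = 0.40, about 40 points. More generally, at 60% cure (assumed) and *n* per arm, 1.96 × √(2 × 0.24/n) gives 43 points for n = 10 and 25 points for n = 30.

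**The case against.** The best defence is that the window is a deliberate proxy for severity at presentation. Section 9.3.1 does not count pneumonia deaths in the first 48 hours as failures, so the protocol seems to treat very early events as belonging to the disease. The trial is also double-blind, no margin or test is set specifically for this subgroup in Sections 11.3.4 and 11.3.5, and any plausible bias is small beside the sampling error shown above.

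Part of this stands. The window has an intelligible purpose, blinding limits bias in the decision to ventilate, and the subgroup would support little inference under either definition. But a rule about attributing deaths does not turn ventilation at hour 36 into a baseline characteristic, and blinding does not remove a drug effect on the need for ventilation. Poor precision is no reason to keep a definition that adds an avoidable bias.

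A reader might also infer four stronger things that the document does not support:

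- *That the bias flatters the drug with more early deterioration.* This needs newly ventilated subjects to have the better prognosis; exchanging the assumed cure rates reverses the sign.
- *That ventilation at entry is an inclusion criterion and so a ready baseline variable.* It is one alternative within one sign, and hypoxemia alone also satisfies that sign.
- *That the change is wording only because ventilation is already recorded.* The Time and Events Schedule has no ventilation item, the baseline signs in Section 9.3.1 omit it, and Section 9.6 mentions intubation only as an example of resource-use data, without a start time.
- *That new ventilation by 48 hours must become an additional ITT outcome.* That would be informative but is not needed to cure the defect.

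**Conclusion.** The point holds. The ventilated subgroup is defined partly by what happens after randomization and after dosing begins, so its two between-arm comparisons lack the protection of randomization. This follows from the protocol's own timing and needs no assumed rate.

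The size does need assumptions: the -3.0 to +5.0 points are an illustration, not an estimate. The bias is zero if the arms do not differ in early ventilation, and small if nearly all ventilated subjects are ventilated at entry. It can go either way. The primary endpoint, its coprimary populations and the noninferiority conclusion are untouched. The definition should be corrected because the defect affects two stated secondary objectives and can be removed at modest cost.

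**What to change.** In the Synopsis (objectives and efficacy criteria) and Sections 2, 9.4 and 11.3.2, define the subgroup for both parameters as subjects mechanically ventilated before the first dose of study drug. If a 0 to 48 hour ventilated group is still wanted, present it by arm as descriptive only, with no between-arm claim.

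The costs are two. The subgroup becomes smaller, so an already imprecise comparison becomes less precise. And the sponsor must confirm that the case report form captures ventilation status, or its start time, relative to the first dose; if it does not, that item has to be added. Because ventilation is not a stratification factor, chance imbalance between arms remains possible, but systematic selection by treatment does not.
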